## Abstract

**Background:**

Inflammatory Bowel Disease (IBD) patients report poorer quality of life (QoL) and more anxiety and depressive symptoms than controls from the general population. Cognitive behavioral therapy (CBT) is effective for anxiety and depression, but questionable in case of co-morbidity with IBD. Therefore, an adapted new CBT specifically designed for IBD patients was developed. The objective of this study is to evaluate the effectiveness of adapted CBT on QoL.

**Methods/design:**

IBD patients with a poor level of mental QoL (score less than or equal to 23 on the mental health scale of SF-36) will be randomly assigned to the experimental (n = 40) or waiting-list control condition (n = 40). The experimental condition will then immediately start CBT. The waiting-list control condition will wait 3,5 months before CBT begins with pre- and post assessments. Both conditions will complete a baseline and follow-up assessment following CBT and a mid-treatment assessment. The primary outcome is IBD-specific QoL (IBDQ). Secondary outcomes are generic QoL (SF-36) and anxiety and depression complaints (HADS, CES-D). Additionally, we will examine the working mechanism of the psychological intervention by investigating the impact of the intervention on illness-related cognitions, attitudes, coping styles and their associations with outcome. Data will be analysed on an intention to treat (ITT) as well as treatment completer basis (greater than or equal to five sessions followed).

**Discussion:**

If found effective, this IBD-specific CBT is a first step to enhance poor QoL in IBD patients and possibly, other gastroenterological diseases. By enhancing IBD patients’ QoL, we may also improve their mental and physical health, and lower unnecessary health care consumption.

**Trial registration number:**

NTR (TC = 1869)

## Background

According to the 2010 international Inflammatory Bowel Disease (IBD: Crohn’s disease and ulcerative colitis) task force meeting, incidence and prevalence of IBD is steadily increasing worldwide [1]. However, in high-incidence regions such as North America, the United Kingdom and Northern Europe the rates of IBD have stabilised [1,2]. In 2000, the incidence and prevalence of CD in North America were approximately 8 and 174 per 100,000, respectively and for UC approximately 8 and 214 per 100,000 respectively [3]. In Northern Europe these figures are slightly lower [2]. Approximately 50,000 people in the Netherlands have medically confirmed IBD. Each year this group increases with 2500 new patients [4]. IBD cannot be cured and the exact cause is unknown. The course of the disorder varies in severity but is characterized by unpredictability and is accompanied by physical symptoms such as diarrhoea, bowel spasms, faeces containing blood or mucus, qualms and fever attacks. Additionally, the medical treatments that, in some cases require life-long administration, often induce side effects and complications, such as weight gain, a moon face, eczema and acne. Peri-anal complications such as abscesses and fistulas severely affect quality of life by impairing sexual function and faecal continence and are a cause of chronic pain. Other manifestations such as spondylarthropathy may cause significant morbidity. Furthermore, many patients require surgical treatment in the course of their disease. Surgery frequently results in a permanent ileostoma or colostoma [5,6]. Moreover, chronic immune suppression that results from medical treatment increases the risk of hematological malignancies. Finally, since IBD is associated with an increased risk of colorectal cancer, patients undergo frequent endoscopic surveillance [7].

Consequently, the quality of life of IBD patients is impaired. Individuals with IBD have been found to report poorer quality of life and more anxiety and depressive symptoms than comparison-controls from the general population [8,9]. Many IBD patients are confronted with fatigue, pain, embarrassment and physical disablement that have negative effects on social and work life. Poor quality of life in turn, has a negative impact on relapse and disease activity [10].

Recent studies and clinical experience suggest that higher levels of anxiety and depressive symptoms in IBD patients are not only related to disease activity and severity. Individual characteristics also affect patients’ experienced distress, especially those associated with illness-related cognitions and attitudes [11]. Specific IBD-related cognitions (e.g. ‘I will never find a partner because of my colostomy bag’; ‘I can’t have sex because I am dirty’; ‘It makes no sense to invest in new work or personal relations because of the unpredictability of my illness’) and (premorbid) attitudes like perfectionism (‘Everything has to be perfect otherwise I am worthless’), dependency (‘Without the help of others I will not survive’) and mistrust (‘In the end other people will always let me down’) are highly influential in terms of ability to cope with IBD.

Of the psychotherapeutic intervention techniques that have been investigated, the most promising intervention for amending such dysfunctional cognitions and attitudes is cognitive behavioral therapy (CBT) [12]. This therapy posits that individual’s biased information processing leads to restrictive thoughts, feelings and behaviors that can culminate in anxiety and depressive symptoms and eventually in psychiatric disorders. CBT offers a well-developed intervention protocol that has been found to enhance quality of life and to decrease psychological distress. It has been found to be effective in people with other chronic illnesses such as chronic obstructive pulmonary disease, diabetes [13], and cancer [14].

A recent meta-analysis of 21 studies was conducted that evaluated the effect of psychological treatment on quality of life, emotional status and disease activity in IBD [15]. The psychological treatments included psycho-education as intervention (10 studies), stress management (3 studies), psychotherapy (6 studies) and other non-specific techniques like a support group (2 studies). Of all included studies only 6 studies evaluated the effect of a multi modular approach including IBD psycho-education (4 of them included CBT techniques). Overall, no significant effects of psychological interventions were found on improving health related quality of life, emotional problems and disease activity. All studies included suffered from various methodological shortcomings such as small sample sizes and non-random sampling. Moreover, all but one study included patients who did not have elevated levels of distress, thereby diluting the treatment effect. Patients in these studies seemed relatively healthy, so perhaps there was no room for improvement. Inclusion of patients with higher anxiety and depressive symptoms may have resulted in more positive effects. Only one study selected patients based on HADS anxiety levels [16]. Given these methodological shortcomings and the many multi-component interventions, it is still unclear what the effects of a specific CBT are. We have, therefore, developed a CBT that is specifically designed for patients with IBD who have a poor quality of life, thereby targeting a patient group that is most burdened by the illness.

We will examine the effectiveness of CBT in this study by using a randomized waiting-list control design, including a sufficiently large number of patients who have elevated levels of mental distress. This paper contains a detailed description of the design of this randomized controlled trial investigating the effectiveness of CBT specifically designed for IBD patients.

### Trial objectives and purpose

The primary objective is to investigate the effectiveness of individual CBT in a sample of IBD patients. Our primary outcome is the effect on IBD-specific quality of life (IBDQ). The secondary outcome is the effect of CBT on generic quality of life (SF-36), anxiety and depression complaints (HADS, CES-D) and illness activity (P-HBI and P-SCCAI). The secondary objective is to investigate the extent to which changes in quality of life and anxiety and depression are mediated by improvements in cognitions, attitudes and coping styles.

Our primary hypothesis states that cognitive behavioral therapy will improve quality of life, and reduce anxiety and depression. Our secondary hypothesis states that improvements in quality of life are mediated by changes in illness cognitions, attitudes and coping styles (avoidant and problem solving coping).

## Methods and design

The present study is a multi-center randomized clinical trial (see Figure 1). All patients with ulcerative colitis or Crohn’s disease attending the out-patient departments of the Academic Medical Center (AMC), VU University Amsterdam (VUmc), Flevo-hospital and Slotervaart-hospital will complete a 36-item questionnaire assessing generic health-related quality of life or health status (SF-36) prior to the consultation. This questionnaire will be administered as part of standard care. The nurse practitioner will be present and can be contacted for further information and help. Patients who score at or below the cut-off score of 23 on the mental health subscale will be eligible for the study [17]. If these patients are also 18 years or older, have a diagnosis of Crohn’s disease or ulcerative colitis and have sufficient command of Dutch, they will be given the informed consent letter by their treating gastroenterologist. After one week they will be contacted by telephone by the researcher to provide further information and/or clarification if needed. Also the researcher will check whether informed consent is received. If patients agree to participate, an appointment will be made to sign the informed consent letter in the presence of the researcher. Participants will be globally screened based on main study inclusion criteria (i.e. physically and mentally able to attend eight weekly sessions and willing to give written informed consent) and exclusion criteria (i.e. current treatment with psychotherapy). During this meeting an appointment will be scheduled for the administration of the Structural Clinical Interview for DSM-IV Disorders-I (SCID-I) that assesses Axis-I psychiatric diagnoses to determine further psychiatric exclusion criteria and to examine psychiatric disorders within this population (for instance anxiety and depression disorders) [18]. Patients will be further excluded from the study if they have current substance dependence or abuse, or psychosis.

**Figure 1 F1:**
[figure not shown]
Flow chart study design.

The SCID-I will be administered by telephone, by psychologists who received a specific training for this.

All patients will then be asked to complete a set of questionnaires that assess the baseline primary and secondary outcomes via the web (see Table 1). If patients prefer paper and pencil completion, these questionnaires will be sent. After completion of the first baseline assessment, patients will be randomly assigned to the experimental or waiting-list control condition. Randomization will be stratified by gender, disease type and type of medical center (peripheral or academic) and will be performed by an independent employee at the Department of Clinical Epidemiology and Biostatistics of the AMC.

**Table 1 T1:** Overview assessment schedule

**Measure**	**Description**	**T**_**baseline**_	**T**_**follow-up after waiting/baseline before CBT**_	**T**_**mid-treatment**_	**T**_**follow-up after CBT**_
*Screening SCID*-*I*^*^	DSM-IV-TR				
	Axis I disorders				
*Primary Outcome*					
IBDQ^**^	Inflammatory Bowel Disease Questionnaire	E C	C	E C	E C
*Secondary Outcome*					
SF-36^**^	MOS 36-item Short-Form Health Survey	E C	C	E C	E C
HADS^**^	Hospital Anxiety and Depression Scale	E C	C	E C	E C
CES-D^**^	The Center for Epidemiologic Studies Depression Scale	E C	C	E C	E C
P-HBI^**^	Patient-based Harvey Bradshaw Index	E C	C	E C	E C
P-SCCAI^**^	Patient-based Simple Clinical Colitis Activity Index	E C	C	E C	E C
*Potential Mediators*					
DAS^**^	Dysfunctional Attitude Scale	E C	C	E C	E C
IPQ-R^**^	Illness Perception Questionnaire-Revised	E C	C	E C	E C
UCL^**^	Utrechtse Coping Lijst	E C	C	E C	E C

*Experimental Condition* (*E*) *and Waiting list Control Condition* (*C*).

^***^*Interview that is administered by telephone.*

^****^*Web-based questionnaire.*

Participants assigned to the experimental condition will start treatment as soon as possible (maximum within 6 weeks). The second, mid-treatment assessment will take place four weeks following start of treatment and the third assessment one month following completion of treatment. Following the first baseline assessment, participants assigned to the waiting-list control condition will wait 3,5 months before they are treated with CBT. This period corresponds to the duration of the CBT intervention and follow-up assessment of the experimental group. After this 3,5 month waiting period the participants in the waiting-list control condition will be asked to complete a follow-up after waiting/baseline before CBT assessment before starting treatment. Analogous to the procedure in the experimental condition, the mid-treatment assessment will take place four weeks following start of treatment and the follow-up assessment one month following completion of treatment (see Table 1).

### Cognitive behavioral treatment manual

The treatment will consist of eight weekly sessions, each lasting one hour. The first session will focus on the rationale of cognitive behavioral therapy, i.e. the influence of (irrational or dysfunctional) cognitions and attitudes on (restrictive) feelings and behaviors. Additionally, goal setting will be initiated. Since patients may have a wide diversity of psychiatric problems (i.e. PTSD, anxiety disorders and depression), the treatment manual will encompass five optional modules for the therapist that focus on each of these disorders (i.e. exposure based for anxiety and PTSD, behavioral activation for depression). The subsequent sessions (2–6) will target teaching the patient to identify and challenge dysfunctional cognitions and attitudes related to IBD. Each session will address specific illness-related cognitions. If possible, dysfunctional cognitions and attitudes will be replaced by helpful cognitions and attitudes. Clearly, some of the dysfunctional cognitions are realistic and reflect the limitations that the disease imposes. Such thoughts will be worked through and intervention will focus on acceptance of these disease limitations. Finally, in the last two sessions, the newly learned cognitions and attitudes will be consolidated using specific CBT techniques such as flashcards with helpful cognitions or attitudes. As customary within CBT, each session patients will be given homework. The CBT will be conducted by registered psychotherapists, specialized in cognitive behavioral therapy.

All treatment sessions will be audio-recorded and therapists will receive feedback over the first two CBT treatments to promote treatment integrity. Additionally, regular supervision will be provided.

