### Sample size

We will consider a difference of 0.5 standard deviation, which is equal to a moderate effect size [29], clinically relevant. For calculating the required difference on the Inflammatory Bowel Disease Questionnaire (IBDQ), we will use the data from a study by McColl et al [30] among 111 IBD patients. The mean IBDQ score was 182 and the standard deviation was 59. A 0.5 standard deviation thus equals approximately 30 points on a scale ranging from 32 to 224. With an effect size of 0.5 standard deviation, an alpha level of 0.05, and a power of 80%, at least 34 patients in both the experimental condition and the waiting list control condition are needed. Given a potential attrition rate of 10%, we will include 40 patients in each condition.

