### Statistical analysis

Analyses of covariance will be conducted to determine the extent to which treated patients (experimental condition) show more improvement on the primary and secondary outcome variables compared to patients in the waiting-list control condition. A two-way factorial analysis of variance with the between-factor condition (experimental condition versus waiting list control condition) and the within-factor assessments will be used. Moreover, stratification variables, i.e. gender, treatment center and disease type will be included as covariates in the analyses (ANCOVA).

Additionally, the data of experimental and the waiting-list control condition will be pooled, to measure the overall effect of treatment. Before the two groups will be pooled, we will examine whether there is a difference in effect for the experimental versus the waiting-list control condition (Delta T_follow-up after CBT_-T_baseline before CBT_). In case differences emerge, this will be stratified reported.

For therapy effects, data will be analysed on an intention to treat (ITT) as well as treatment completer basis. The completers sample will include patients who attend at least 5 CBT sessions.

To express the magnitude of the effects, mean gain scores on the outcome measures will be standardized to Cohen’s *d*, representing the number of standard deviations separating the two means. Point estimates and 95% confidence intervals of *d* will be determined for the within and the between group effects. Between effect sizes will be calculated using the pooled standard deviation (of the baseline scores) and confidence intervals will be approximated from the central *t*-distribution.

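### The stated ANCOVA and the interval for Cohen's d make no allowance for therapist clustering in the CBT arm, so the interval will be too narrow if outcomes differ between therapists

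*Protocol article*

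**What the plan says.** **Delivery.** Under Cognitive behavioral treatment manual, the protocol article describes individual sessions and states: "The CBT will be conducted by registered psychotherapists, specialized in cognitive behavioral therapy". The plural means more than one therapist; neither their number nor their caseload is given. The section adds: "All treatment sessions will be audio-recorded and therapists will receive feedback over the first two CBT treatments to promote treatment integrity". Feedback on the first two treatments suggests that a therapist treats more than two patients. Regular supervision is also planned. The manual has optional modules, which the article links to the range of psychiatric problems that patients may have.

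**Control arm.** Under Methods and design, waiting-list patients wait 3.5 months before CBT. They have no therapist during the randomised comparison.

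**Analysis.** Under Statistical analysis, the model has condition as between-patient factor and assessment as within-patient factor, and "stratification variables, i.e. gender, treatment center and disease type will be included as covariates in the analyses (ANCOVA"). The between-group Cohen's d is scaled by the pooled baseline SD, with a confidence interval from the central t-distribution. The two conditions are later pooled to estimate an overall treatment effect.

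**Sample size.** The calculation reads "With an effect size of 0.5 standard deviation, an alpha level of 0.05, and a power of 80%, at least 34 patients in both" arms, followed by "Given a potential attrition rate of 10%, we will include 40 patients in each condition". It contains no design effect.

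**The concern.** Patients of one therapist share that therapist's skill and style, so their outcomes may be more alike than those of patients of different therapists. If so, 40 experimental patients carry less information than 40 independent ones, and the variance of the CBT arm mean is larger than the planned model assumes. The control arm is unaffected. This is a partially nested design, analysed by a model for fully independent patients.

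The listed covariates do not close the gap. The article states no link between therapists and hospitals, and randomisation distinguishes only academic from peripheral centers. In any case, a center effect common to both arms cannot absorb variation that exists in the CBT arm alone.

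At stake are the standard error, p-value and 95% interval for the main IBDQ comparison, and the extent to which the result can be read as a property of the treatment rather than of the therapists who happened to deliver it. The second matters here because the Feasibility section names future dissemination as an aim, which means delivery by other therapists.

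**Working it through.** **The plan's own figure.** The article gives no figure for clustering. Its only related number is 34 per condition. The two-group formula with the stated inputs gives 2 x (1.960 + 0.842)^2 / 0.5^2 = 62.8, so 63 per arm two-sided (50 one-sided). A paired t-test gives 33.4, rounded up to 34. An ANCOVA gives 34 only with a baseline correlation near 0.68, which is not stated: 62.8 x (1 - 0.68^2) = 33.8. So 34 does not follow from the stated two-group inputs. That is a separate matter and is not used below. Here it matters only that none of these routes leaves room for a design effect.

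**Inputs from the article.** 40 patients per arm (Sample size); clusters in the CBT arm only (Methods and design; Cognitive behavioral treatment manual); no therapist term (Statistical analysis).

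**Assumptions.** k = 2, 4 or 8 therapists with equal caseloads; ICC 0.01, 0.05 or 0.10; the same total variance in both arms.

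**Formulas.**
- Caseload m = 40/k
- Design effect in the CBT arm, DE = 1 + (m - 1) x ICC
- Correct SE of the difference / model SE, f = sqrt((1 + DE)/2), because only one of two equal arms is clustered
- Coverage of the nominal 95% interval = 2 x Phi(1.96/f) - 1

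**Worked case, k = 4, ICC 0.05.** m = 10; DE = 1 + 9 x 0.05 = 1.45; f = sqrt(2.45/2) = 1.107; 1.96/1.107 = 1.77; coverage 92.3%.

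| Therapists | ICC | DE | f | Coverage |
|---|---|---|---|---|
| 8 | 0.01 | 1.04 | 1.010 | 94.8% |
| 4 | 0.01 | 1.09 | 1.022 | 94.5% |
| 2 | 0.01 | 1.19 | 1.046 | 93.9% |
| 8 | 0.05 | 1.20 | 1.049 | 93.8% |
| 4 | 0.05 | 1.45 | 1.107 | 92.3% |
| 2 | 0.05 | 1.95 | 1.214 | 89.3% |
| 8 | 0.10 | 1.40 | 1.095 | 92.6% |
| 4 | 0.10 | 1.90 | 1.204 | 89.6% |
| 2 | 0.10 | 2.90 | 1.396 | 84.0% |

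With ICC = 0, f = 1 and nothing changes. With 36 per arm (40 less 10% attrition) the figures barely move: k = 4, ICC 0.05 gives f = 1.095.

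**Check by simulation.** A t-test that ignores therapist (40,000 runs, 40 per arm, therapist effects averaging to zero) rejected in 5.1% of runs with ICC 0; 5.1% with k = 8, ICC 0.01; 6.0% with k = 8, ICC 0.05; 7.4% with k = 4, ICC 0.05; 10.4% with k = 4, ICC 0.10; and 10.6% with k = 2, ICC 0.05. One minus the tabled coverage gives 5.0% (ICC 0), then 5.2%, 6.2%, 7.7%, 10.4% and 10.7%, in close agreement.

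**Pooled pre-post analysis.** All 80 patients are then treated. If the same therapists serve both arms, m = 80/k and no unclustered arm dilutes the effect, so f = sqrt(DE). With ICC 0.05 for the change scores: k = 8 gives DE = 1 + 9 x 0.05 = 1.45 and f = 1.20; k = 4 gives DE = 1 + 19 x 0.05 = 1.95 and f = 1.40.

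**The case against.** The best defence is that this is an omission in a condensed article, and that a therapist term may appear in a full protocol or analysis plan that is not shown. That may be so. But the article does not stop at naming a model family: it lists the factors, the covariates and the construction of the interval. That stated analysis does not match the delivery structure stated a few sections earlier.

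Three other objections stand and limit the point:
- **Size.** With many therapists and a small ICC the loss is negligible. A reader might infer that the interval is definitely too narrow; the article gives neither the number of therapists nor any sign of the ICC, so only the conditional statement is supported.
- **Null hypothesis.** Controls have no therapist, so the clustering arises through treatment. If CBT changed nobody's outcome, no such clustering would arise and the nominal 5% would hold. The inflated error rates apply only when therapist effects differ but average to zero.
- **Target of inference.** A random therapist effect is needed to generalise beyond these therapists; a conclusion limited to them does not require it. The stated interest in dissemination favours the wider target, but the analysis section does not say which is meant.

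A reader might also infer that differences in delivery are built in, because therapists have optional modules and feedback covers the first two treatments. The article does not support this. The modules are tailored to patients' disorders and are not in themselves evidence of clustering. All sessions are recorded and supervision continues, which may reduce therapist differences, although it does not model them.

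**Conclusion.** The point holds in conditional form, as a cheap improvement rather than a demonstrated error in the result. The stated model and interval assume independent patients in an arm that is nested within therapists, and none of the listed covariates can stand in for therapist.

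The tabled range, from a standard error 1% too small to one whose correct value is 40% larger, rests entirely on the assumed number of therapists, equal caseloads and ICC. The loss is material with 2 to 4 therapists and an ICC of 0.05 or more, and trivial with 8 therapists and an ICC of 0.01. The pooled analysis is more exposed than the randomised comparison if the same therapists treat both arms.

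**What to change.** 1. Record the treating therapist for every patient, and report the number of therapists and their caseloads.
2. Analyse the IBDQ with a partially nested model: the stated fixed effects and covariates, a random therapist effect in the CBT arm only, each control as a singleton, and small-sample degrees of freedom. Base the interval for the between-group d on this model's standard error and degrees of freedom.
3. Fix in advance, before outcome data are seen, the number of therapists below which the variance component is considered too unstable. In that case keep the stated ANCOVA as primary and report the partially nested model as a prespecified sensitivity analysis, with the mean change for each therapist.
4. Apply the same approach to the pooled pre-post analysis, with a therapist effect for all treated patients.

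The cost is one recorded variable and one model term. Treatment, visits and recruitment numbers do not change. The downside is a somewhat wider interval, and an imprecise variance component when therapists are few.
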